**Figure 4 Fig4:**
[figure not shown]
Logic model of enhanced rehabilitation intervention following proximal femoral fracture.

**Figure 5 Fig5:**
[figure not shown]
Mapping the rehabilitation intervention to the NICE recommendations for the management of hip fracture.

#### Delivery of the intervention

The intervention will be delivered by the therapists and their assistant staff employed by BCUHB. The therapy service managers in BCUHB have agreed to organise the extra sessions for patients in the intervention arm of the study, which will be funded by NHS excess treatment costs. The extra six sessions of rehabilitation will be delivered by additional physiotherapists and therapy assistants. This will be done in collaboration with the existing therapists delivering the usual care. The intervention therapy teams will be alerted to which group the patient is randomised and will arrange a time for an initial assessment and goal-setting session to visit the patient in the acute hospital or in a community setting. The remaining five sessions will be used according to individual’s need and the individual’s rehabilitation plan.

#### Randomised feasibility study outcomes

The outcomes will be collected in a variety of ways. Demographic data will be collected from patients and their records. Recruitment rates will be collected by researchers from their screening and recruitment records. At baseline and 3 months follow-up, patient-completed outcome measures will be completed by participants, assisted by NISCHR CRC professionals or a member of the research team who will be blind to treatment allocation. Participants will also be given the choice to complete validated versions in Welsh where they exist. At baseline, fewer patient-completed outcome measures will be used than at 3-month follow-up as we wish to reduce the burden on patients at a time shortly after surgery. Physical function will be objectively assessed by the researcher at baseline using the grip strength test. At 3 months follow up, a physiotherapist will measure other objective tests of physical function, including the grip strength test. These will be performed in the physiotherapy gym or if the patient is unable to travel in their own home. The timing of outcome assessments is summarised in Table 1.

**Table 1 Tab1:** FEMuR protocol schedule of forms and procedures

Event	Baseline	Timeline post randomisation		
		During 3 months	At 3 months	Post 3-month follow-up
Eligibility screening and consent for randomised feasibility study				
Patient	X			
Carer	X			
Outcome measurement for feasibility study				
Cognitive status				
•AMTS [25]	X			
Primary				
•Barthel index [27]	X		X	
Secondary				
•NEADL Scale [28]	X		X	
•HADS [29]	X		X	
Process				
•VAS for hip pain [30]	X		X	
•GSES [32]	X		X	
•FES-I [33,34]			X	
•SES [35]			X	
•VAS-FoF [36]			X	
Health economic				
•EQ-5D 3L [37]	X		X	
•ICECAP-O [38,39]	X		X	
•CSRI [40]	X		X	
•DCE [43]			X	
Physical				
•Grip strength [45]	X		X	
•30-s sit-to-stand [46,47]			X	
•8-ft (2.5 m) get-up-and-go [47]			X	
•50-ft (15.4 m) walk [48]			X	
Carer strain index	X		X	
Therapist process outcomes and use of the intervention workbook				
•Date of extra session		X		
•Whether the session is face to face or indirect		X		
•Where the face to face session is held		X		
•If the session is face to face, time is spent on assessment, exercise, ADL practice, working on the workbook etc.		X		
Qualitative follow up patients and carers focus groups/individual interviews - (invited)				
Patients			X	X
Carers			X	X
Recruitment and consent of staff to focus groups		X	X	X

#### Routinely collected demographic, clinical and recruitment data

During recruitment to the feasibility study, we will collect information on the number of patients approached, the number eligible, the number who did and did not consent, and where possible the reasons why. The number of eligible patients who fulfilled the inclusion criteria and were willing to be randomised will be expressed as a percentage of the numbers in the cohort dataset. In addition, we will record the number who withdraw after baseline assessment and randomisation, and the number who complete the various outcome measures at baseline and 3 months follow-up. The researchers who administer the outcome measures will record the reasons for any non-completion.

The following demographic data and descriptors will be collected:Date of birth (age)GenderType of fractureType of surgeryLiving arrangementsPlace of residence prior to admissionPlace of discharge from acute and/or community hospital

#### Cognitive status

Abbreviated Mental Test Score (AMTS) [25].

The AMTS is a test with evidence of validity that is widely used in clinical and research settings in the UK for detecting and monitoring cognitive impairment. This will be used as a baseline description of the level of cognition. It is brief (ten items) and recommended for cognitive screening in acute settings in the Alzheimer’s Society (2013) tool-kit [26] ‘Helping you to assess cognition: a practical toolkit for clinicians’. It is generally considered to be easily administered and well tolerated by raters and subjects. The score range is 0 to 10 with higher scores indicating worse cognitive function.

#### Patient completed measures - primary outcome

Barthel index [27].

This is a patient- or assessor-completed outcome measure of current functional status measuring individuals’ ability to care for themselves. It has evidence of validity when used in patients with musculoskeletal or neuromuscular disorders and is considered easy to use, reliable and sensitive to change. It focuses on the person’s level of independence on the following items: feeding, bathing, grooming, dressing, bowel function, bladder function, toilet use, transfers, mobility on level surfaces and stairs. It will be measured at baseline and at the 3-month follow-up assessment. The score range is 0 to 20 with lower scores indicating increased disability.

#### Patient completed measures - secondary outcomes

Nottingham Extended Activities of Daily Living (NEADL) Scale [28].

This is a patient-completed outcome measure of activities of daily living from the previous 4 weeks which has evidence of validity in stroke patients. The NEADL is a record of actual activity rather than capability, scoring patients in the areas of mobility, kitchen, domestic and leisure activities. A higher score indicates a greater level of independence. When assessed at baseline, it will assess the participant’s functional capacity prior to hip fracture. It will also be used at the 3-month follow-up assessment to assess the degree of functional recovery. The score range is 0 to 66 with higher scores indicating greater independence.Hospital Anxiety and Depression Scale (HADS) [29].

This is a patient-completed outcome measure of anxiety and depression. It is designed to measure anxiety and depression in patients with physical health problems. It has seven items related to common symptoms of anxiety and seven for depression. Patients are asked whether they experience the symptom definitely, sometimes, not much or not at all. The HADS was designed for use in the hospital setting but has been used successfully with the general population. This measure will be used at baseline and at the 3-month follow-up assessment. The two sub-scales have a range of 0 to 21 with higher scores indicating increased anxiety or depression.

#### Process measures (potential mediators of outcomes)

Visual Analogue Scale (VAS) for hip pain intensity [30].

This is a patient-completed visual analogue scale of current hip pain intensity. Hip pain following surgery is an important factor affecting rehabilitation and will be measured at baseline and at the 3-month follow-up assessment. We have chosen a VAS as there is evidence of validity compared with the Oxford Hip Score [31] whilst being simpler and quicker to complete, thus reducing the burden on patients. The range is 0 to 10 on a segmented line.General Self-Efficacy Scale (GSES) [32].

The GSES is not behaviour specific and is chosen as a measure of general confidence when facing challenge. In order to assess change over time in such expectancy-based cognitions pre and post intervention (as well as test between group differences at follow-up comparing intervention with control), we have chosen this short self-efficacy scale for baseline. It has evidence of validity in the populations of older people and surgical patients. The range is 10 to 40 with higher scores indicating increased self-efficacy. The measure will also be completed at 3-month follow-up with the more behaviour specific Falls Efficacy Scale - International and the self-efficacy for exercise scale (see below).Falls Efficacy Scale - International (FES-I) (self efficacy) [33,34].

The FES-I measures how concerned a patient is about falling when performing activities of daily living both inside and outside of the home. The scale details 16 activities which the patient must rate from 1 (not at all concerned) to 4 (very concerned) with regards to how concerned they would be about falling if they performed the activity. The range is 16 to 64 with higher scores indicating a greater fear of falling. The FES-I has been used successfully in older patients both without and with mild cognitive impairment.Self-efficacy for exercise scale [35].

The self-efficacy for exercise scale is a revision of unpublished self-efficacy barriers to exercise measure. The scale consists of statements regarding the participant’s confidence that they could exercise for 20 min, three times a week, depending on factors such as pain and mood. The participants are instructed to use numbers from 0 (not confident) to 10 (very confident) to rate their expectations. This measure assesses the participant’s present expectations and so will be used only at the 3-month follow-up as pain from surgery would likely be the major factor in these expectations at baseline and would not measure normal levels of self-efficacy for the patient. The range is 0 to 90 with higher scores reflecting more confidence in capability.Visual Analogue Score - Fear of Falling (VAS-FoF) [36].

This is a patient-completed visual analogue scale for fear of falling. A VAS is useful as it is easy to administer and brief. The range is 0 to 10 on a segmented line with higher scores indicating greater fear of falling. It has previously been used in older adults with and without cognitive impairment with good results [25] and will be used to measure fear of falling in our study at 3 months follow-up.

#### Health economic measures

EuroQol EQ-5D (three levels) [37].

This is a patient-completed index of health-related quality of life, which gives a weight to different health states. It consists of five dimensions: mobility, self-care, usual activities, pain/discomfort, and anxiety/depression. Each has three possible responses. The responses record three levels of severity (no problems, some/moderate problems and extreme problems) which is then converted to a health utility weight using UK norms. It will be used at baseline and at the 3-month follow-up assessment and allows the calculation of quality-adjusted life years (QALYs), using area under the curve method which will be used as part of the economic analysis.ICEpop CAPability measure for Older people [38,39].

This is a patient-completed measure of capability in older people that focuses on well-being rather than health. It comprises five attributes: attachment (love and friendship); security (thinking about the future without concern); role (doing things that make you feel valued); enjoyment (enjoyment and pleasure); and control (independence). Each attribute has four possible responses. The responses record the extent of capability (all, a lot, a little, and none), and the five-digit outcome is converted to capability utility derived from UK norms. It will be used at baseline and at the 3-month follow-up assessment as part of the economic analysis.Client service receipt inventory (CSRI) [40].

The CSRI is a questionnaire for collecting retrospective information about study participants’ use of health and social care services, including voluntary services (e.g. charity services), including the components of the rehabilitation programme. This information will be combined with national sources of reference unit costs [41,42] in order to calculate health and social care service costs for the economic evaluation. It will be used at baseline and at the 3-month follow-up assessment as part of the economic analysis.Discrete choice experiment [43,44].

A discrete choice experiment (DCE) [43,44] will explore participants’ preferences for rehabilitation services. Hypothetical rehabilitation services (A and B) will be presented to each participant according to a set number of characteristics, each of which has different levels. These characteristics and levels will create a set of alternative scenarios. In each scenario, the participant will be asked which service they prefer by ticking ‘A’ or ‘B’. The characteristics and levels will be chosen for the DCE based upon the outcomes of the literature review and focus groups conducted in phase I of the study. It will be used at the 3-month follow-up assessment as part of the economic analysis.

#### Objective measures of physical function

Grip strength [45].

This is an objective measure of physical function that will be administered by the researcher administering the patient-completed questionnaires. Grip strength correlates well with general fitness and muscle strength relating to physical function. It is also a more appropriate measure for use at baseline, as performing other physical assessments may carry risk to patients at this time point or would be likely to primarily reflect post-operative pain and not overall function. Grip strength will be measured at baseline and at the 3-month follow-up assessment. Other objective measures will be administered by a physiotherapist at the 3-month follow-up and are listed below:Thirty-second sit-to-stand [46,47].

From a seated position in a chair with no armrests, the participant rises to a full stand and returns to a fully seated position without using their arms to support themselves. An observer measures the number of stands completed in 30 s. The 30-s sit-to-stand is used to measure lower body strength and is useful in older adults because it is part of everyday activities, e.g. getting off the toilet and getting in and out of a car and a chair. It correlates reasonably well with other measures of lower body strength such as knee extensor and knee flexor strength and has been shown to have good test-re-test reliability in older adults living in a community setting [46,47].Eight-foot (2.5 m) get-up-and-go test [47].

Timed up-and-go test (also known as ‘8 get-up-and-go’) is used to assess mobility, agility and balance. An observer measures the time taken for a participant to stand up from a chair, walk 8 ft (2.5 m) with or without a walking aid, turn 180°, walk back to the chair and sit down. There is evidence of validity and reliability [33-36].Fifty-feet (15.4 m) walk test [48].

The participant is brought to start on a level 50-ft (15.4 m) walk test course (25 ft out and 25 ft back) and is asked on the command ‘go’ to walk as quickly as possible to the 25-ft (7.7 m) mark and back. An observer records the amount of time taken from the command ‘go’ until the starting line is crossed on the way back. It has been shown that there are correlations between the recorded gait time and muscle strength and also with the ability of older people living in the community to carry out activities of daily living [49].

#### Carer completed measure - secondary outcome

Caregiver strain index [18].

Carers who have been recruited onto the study will be asked to complete this measure. It is a 13-item tool that measures strain related to care provision. There is at least one item for each of the following major domains: employment, financial, physical, social and time. Positive responses to seven or more items indicate a greater level of strain. It can be used to assess individuals of any age who have assumed the role of caregiver for an older adult. It will be completed at baseline and at the 3 months follow-up. The range is 0 to 13 with a higher score indicating greater strain.

#### Therapist process outcomes and use of the intervention workbook

In order to describe the rehabilitation programme in both arms of the feasibility study, we will access routinely collected data that therapists complete on their ‘Therapy Manager System’. An information technology manager at BCUHB will extract the following data and return them anonymously to the research team, identifiable only by participants’ study ID. The intervention therapy teams will complete a paper record of how they use the extra sessions which also form part of patients’ clinical records. A BCUHB member of staff will extract the following from these records and return it to the research team:Patient study identification, date of extra session;Whether the session is face to face or indirect;Where the face-to-face session is held; andIf the session is face to face, how much time is spent on different aspects such as assessment, exercise, activity of daily living (ADL) practice and working on the workbook.

We will assess whether the fidelity and dose of the enhanced rehabilitation programme delivered to participants is consistent with our programme theory. We will describe how the programme is delivered along with patients’ views and their use of the workbook which will be collected through focus groups described later. The workbook contains a page of questions and Likert scale type response options to encourage participants to provide feedback on their workbook. Researchers will also collect the diary sections to assess how they are used. We will evaluate engagement with the workbook by counting how many diaries are used, how regularly they are filled out, and whether goals are set and quizzes completed.

#### Triangulation study of service use information

The health service use data obtained from the patient completed CSRI questionnaires will be compared with the same information obtained from routinely collected data recorded on computerised patient records. The data will be collected by NWORTH and BCUHB IT staff.

### Assessment of safety

#### Recording adverse events

All adverse events will be recorded in this study. There are adverse events (AEs) and serious adverse events (SAEs). Adverse events will include the following:Non-injurious falls;An exacerbation of a pre-existing illness;An increase in frequency or intensity of a pre-existing episodic condition;A condition (even though it may have been present prior to the start of the feasibility study) detected after the start of the study; andContinuous persistent disease or symptoms present at baseline that worsens during the study.

The following will not be included as adverse events:Medical or surgical procedures where the condition which leads to the procedure is the adverse event;Pre-existing disease or conditions present before treatment that do not worsen; andOverdose of medication without signs or symptoms.

SAE will be any medical event that:Results in death;Is life-threatening (refers to an event during which the participant was at risk of death at the time of the event; it does not refer to an event which might have caused death had it been more severe in nature);Falls and repeat fractures;Requires hospitalisation or prolongation of existing hospitalisation;Results in persistent/significant disability or incapacity; andOther important medical events that, based upon appropriate medical judgement, may jeopardise the participant and may require medical or surgical intervention.

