#### Cohort study outcomes

From the cohort anonymised data set, we will record the following:The number of patients aged over 65 years admitted with a proximal femoral fracture.The number of patients who fulfil the inclusion criteria for the randomised feasibility study.The number of deaths, serious complications such as falls and repeat fractures, serious illness requiring hospital re-admission and discharged to institutional care. This will include details such as the type of ward and the type of residential care in order to calculate the cost per night locally. This will be compared with the Department of Health reference costs for proximal femoral fracture related hospital stays.

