#### Process for recording adverse events

All adverse events will be recorded by researchers when they are made aware of the event by the patient, carer, the treating clinicians, or therapists. Adverse event reporting information will be included in the training given to the therapy teams delivering the intervention and they will be given copies of the adverse event reporting forms (Additional file 3) and details of how to return them to the research team. Details of the adverse event reporting procedure will also be included in letters to the participants’ GP and consultant informing them of their participation in the study. The adverse event form will have two sections, the first is for the healthcare professional to complete and return to the study manager. The study manager will liaise with the chief investigator who will determine whether the adverse event is serious or not and whether it is related to the study. The chief investigator will complete the second part of the form. All serious adverse events, along with the chief investigator’s assessment of whether it is related to the study, will be sent to the Data Monitoring and Ethics Committee (DMEC) for a second opinion. The trial study manager will record the information on the study master file and inform the clinical trials unit manager. Study-related serious adverse events will be reported to the sponsor and to the academic school (Schools of Medical and Healthcare Sciences, College of Health and Behavioural Science) within 24 h of being determined as serious. They will also be reported to the DMEC chair and the research ethics committee.

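### A non-injurious fall meets both the adverse event and the serious adverse event definition, and only the intervention arm has an additional, trained route for reporting events

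*Protocol article*

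**What the plan says.** The section on recording adverse events gives two lists. The first, for adverse events, opens with "Adverse events will include the following:Non-injurious falls". The second, for serious adverse events, includes "Falls and repeat fractures;Requires hospitalisation or prolongation of existing hospitalisation", where falls stand without any reference to injury. The cohort study outcomes also speak of "serious complications such as falls and repeat fractures", again unqualified.

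The section on the process for recording adverse events sets out how events arrive: "All adverse events will be recorded by researchers when they are made aware of the event by the patient, carer, the treating clinicians, or therapists". On preparation for reporting it says: "Adverse event reporting information will be included in the training given to the therapy teams delivering the intervention". Those teams also receive the forms and return instructions. The GP and consultant of each participant are told of the procedure by letter. A healthcare professional fills in the first part of the form, and the chief investigator decides on seriousness and relatedness. All serious events go to the data monitoring committee for a second opinion. Those judged study-related also go to the sponsor and the academic school within 24 h, and to the committee chair and the ethics committee.

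The delivery section says that service managers will "organise the extra sessions for patients in the intervention arm of the study". There are six such sessions. Table 1 lists no enquiry about adverse events or falls at any time point.

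**The concern.** Two things look wrong, and both bear on falls. Falls are a central safety event for a programme that aims to increase physical practice and reduce fear of falling.

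First, one event can carry two labels. The label has consequences, because only events called serious receive the committee's second opinion and only serious, study-related events are reported within 24 h.

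Second, recording depends on someone speaking up, and one arm has more trained people in contact with patients. If an intervention-arm fall is more likely to be reported than a usual-care fall, the by-arm description will show more falls with the intervention even when the true risks are equal. Identifying adverse events is part of the first study objective, and the abstract names them among the secondary outcomes. The definitive trial would inherit both the figures and the recording method.

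**Working it through.** **Step 1: definitions side by side.** No arithmetic applies here.

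| Event | Meets adverse event entry? | Meets serious entry? |
|---|---|---|
| Fall without injury | Yes, named explicitly | Yes, falls are unqualified |
| Fall with injury | Not named in that entry | Yes |

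The first row is the overlap. No precedence rule is given. The serious entry could be read as meaning injurious falls only, but the text does not say so, and the cohort outcomes again call falls serious without qualification.

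**Step 2: reporting routes by arm.**

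| Route | Intervention | Usual care |
|---|---|---|
| Patient or carer tells the researchers | Yes | Yes |
| GP or consultant, informed by letter | Yes | Yes |
| Usual-care therapists | Yes; no reporting training or forms described | Yes; no reporting training or forms described |
| Intervention therapy team, trained and given forms, up to six sessions | Yes | No |
| Enquiry about events listed in Table 1 | None | None |

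The arms differ in one row only.

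**Step 3: possible size.** The plan gives no figure to reproduce, so this is an illustration.

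- From the protocol: target of 50 participants, allocated 1:1, so 50/2 = 25 per arm.
- Assumed, not in the documents: the same true risk p of at least one fall in both arms; capture probability c_I = 0.90 with the intervention; c_U = 0.50, 0.70 or 0.90 with usual care.

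Expected recorded fallers per arm = 25 × p × c. The apparent ratio is (25 × p × c_I)/(25 × p × c_U) = c_I/c_U, so p cancels. For p = 0.30:

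| c_U | Intervention | Usual care | Ratio |
|---|---|---|---|
| 0.50 | 25 × 0.30 × 0.90 = 6.75 | 25 × 0.30 × 0.50 = 3.75 | 0.90/0.50 = 1.80 |
| 0.70 | 6.75 | 25 × 0.30 × 0.70 = 5.25 | 0.90/0.70 = 1.29 |
| 0.90 | 6.75 | 25 × 0.30 × 0.90 = 6.75 | 0.90/0.90 = 1.00 |

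True risks of 0.20 and 0.40 give the same ratios. The range includes no bias at all.

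**The case against.** Much of the case on the other side stands.

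- A reader might infer that serious-event counts depend on which list the reporter follows. The text does not support this: the chief investigator decides seriousness for both arms, and all adverse events are to be recorded whatever their label. What remains is that the chief investigator has two overlapping entries to apply, so the routing of a non-injurious fall is not fixed.
- A reader might infer that events are captured through therapist contact in one arm only. The text names patients, carers and treating clinicians as well, and informs GPs and consultants in both arms. The intervention team is an additional route.
- A reader might infer that a planned safety comparison is invalid. No specific safety test is set out, and the feasibility criteria contain no safety threshold. What is affected is the by-arm description of adverse events.
- Symmetric sources exist. Both arms complete the service receipt inventory at 3 months, and service use is also taken from electronic records. Admissions, themselves a criterion for seriousness, should therefore be found similarly in both arms. A fall that leads to no service contact would appear in neither source.
- The article condenses a fuller protocol, and the adverse event form is an additional file that is not shown. The 3-month form may already ask about events. That limits the criticism of the missing question, but it does not remove the overlap in the printed lists or the one-sided training that the article describes.

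**Conclusion.** The overlap is a plain contradiction in the text: a non-injurious fall is both an adverse event and a serious adverse event, so its route to the data monitoring committee, and to expedited reporting if study-related, is undetermined. The passages must be reconciled. The documents do not show which class is intended, and this review takes no view on it.

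The unequal reporting route is also in the text. It may bias the by-arm description of adverse events against the intervention, chiefly for minor falls without service contact. The size cannot be derived from the documents. The ratios of 1.0 to 1.8 rest entirely on assumed capture probabilities and equal true risks. The documents do not support the stronger statement that the safety data as a whole are unreliable.

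**What to change.** 1. Reconcile the entries on falls in the two lists, and the wording in the cohort outcomes, so that each fall has one class and therefore one reporting route.
2. At the existing blinded 3-month assessment, ask one identical question in both arms about falls and other events since randomisation, and show it in Table 1. If the form already has such a question, say so in the protocol.
3. Base the main by-arm description on that question together with the service-use and electronic records.
4. Continue to record and report every event from any other source, and tabulate events by source so that therapist reports remain visible without driving the contrast between arms.

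The cost is a change of wording and one more question, with no extra visit. There are limits: recall over 3 months is imperfect, and there will be no prompted answer from participants who are lost to follow-up or lose capacity. The plan accepts retention of 75%, with a minimum of 63%, so 25% to 37% could lack a prompted answer. For them the records and other reports remain the only sources, which is a further reason to keep those in the tables.
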